### Recruitment

Participants will be recruited at or following their first antenatal assessment for ORIGINS. Participants will receive recruitment materials (a recruitment video and website link) via email and/or text message. Interested participants will be directed to the study website to complete electronic consent forms and web-based screening measures via REDCap (Vanderbilt University). In addition to assessing eligibility criteria and parity (for stratification), the screening assessment will include the Edinburgh Postnatal Depression Scale (EPDS). This is a valid tool for detecting symptoms of depression during pregnancy and postnatally [64]. Participants scoring above the thresholds for the risk of depression (total score ≥13) or reporting thoughts of self-harm (score of 1-3 on item 10) will receive a phone call from a registered psychologist to discuss referral to more targeted support services. They will not be excluded from participation in the study.

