### Data Monitoring and Harms

Adverse events will be monitored weekly based on the self-reported data provided by participants at the weekly assessment and the data collected by the ORIGINS team. The key adverse event linked to the MMM study is deteriorating mental health; however, there is also a range of potential adverse events linked to pregnancy that are recorded by ORIGINS. In the MMM study, participants will be encouraged to contact the RA at any point if they have concerns about deteriorating mental health. They are asked weekly if they wish to continue with the program. If they select “no,” they are asked about their reasons for discontinuation (including concerns about their mental or physical health). If participants report concerns about their mental health during the intervention or upon withdrawal from the study, they will be screened for depressive symptoms using the EPDS and for symptoms of traumatic stress using the abbreviated version of the Posttraumatic Stress Disorder Checklist–Civilian version (PCL-C) [82]. Participants who endorse item 10 on the EPDS or score 14 or more on the abbreviated PCL-C will receive a follow-up phone call from the study psychologist to discuss referral to more intensive or specialized support services. If a participant reports concerns about their mental or physical health, this will be reported to ORIGINS. ORIGINS has standard operating procedures for following up adverse events [62]. All adverse events in the MMM study will be recorded on an adverse event monitoring form, and all events and follow-up will be reported to an independent study monitor.

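### An EPDS total of 13 or more prompts a psychologist call at screening but not in the harms pathway, where the EPDS is given again for depressive symptoms

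*Protocol article*

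**What the plan says.** The article gives two rules for when a psychologist telephones a participant.

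- **At entry (Recruitment).** The EPDS is introduced with the statement "This is a valid tool for detecting symptoms of depression during pregnancy and postnatally". The rule covers "Participants scoring above the thresholds for the risk of depression (total score ≥13) or reporting thoughts of self-harm", the latter defined as 1-3 on item 10. These women "will receive a phone call from a registered psychologist to discuss referral to more targeted support services". They stay in the trial.
- **During the trial (Data Monitoring and Harms).** The section states: "The key adverse event linked to the MMM study is deteriorating mental health". It then says: "If participants report concerns about their mental health during the intervention or upon withdrawal from the study, they will be screened for depressive symptoms". The instrument named for this is the EPDS; the abbreviated PCL-C is given as well, for traumatic stress. The call rule is: "Participants who endorse item 10 on the EPDS or score 14 or more on the abbreviated PCL-C will receive a follow-up phone call". The study psychologist makes this call, and its purpose is to talk about onward referral to a higher or more specialist level of care.

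The harms section adds two further steps: "If a participant reports concerns about their mental or physical health, this will be reported to ORIGINS", and all adverse events, with their follow-up, go to an independent study monitor.

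**The concern.** In the harms pathway the EPDS is given to detect depressive symptoms, but the depression score leads to no call. The only EPDS result that does is item 10, which Recruitment identifies as the self-harm item. The trauma score can prompt a call on its own; the depression total cannot.

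On depression, the rule is therefore weaker where there is more reason for concern. At entry a woman with no complaint is called at a total of 13. During the trial a woman who has reported a problem and has the same total is not called on that score.

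The woman most exposed is one who scored below 13 with item 10 at 0 at entry, and so had no call then. If she later reports a concern and scores 13 or more, still with item 10 at 0 and with PCL-C below 14, no call is prompted at either point. Hers is a plain case of the event that the section names as its key harm.

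**Working it through.** No sample size, power or error-rate figure is involved. The check compares the two rules.

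**Inputs**

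- Recruitment: call if EPDS total ≥13, or item 10 = 1-3.
- Data Monitoring and Harms: call if item 10 is endorsed (≥1), or abbreviated PCL-C ≥14.
- Sample Size: 25 per arm, 3 arms.
- Table 3: the EPDS has 10 items.

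**Step 1: count the triggers.** Recruitment has 2 EPDS triggers. The harms section has 1 EPDS trigger plus 1 PCL-C trigger. EPDS triggers not carried over: 2 − 1 = 1, the total. Triggers added: 1, the PCL-C.

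**Step 2: apply both rules to women with EPDS total ≥13.** Item 10 (0 or ≥1) and PCL-C (<14 or ≥14) give 2 × 2 = 4 combinations.

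| Item 10 | PCL-C | Screening EPDS rule | Harms rule |
|---|---|---|---|
| ≥1 | ≥14 | call | call |
| ≥1 | <14 | call | call |
| 0 | ≥14 | call | call |
| 0 | <14 | call | **no call** |

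The harms rule prompts a call in 4 − 1 = 3 of the 4 combinations; the screening rule does so in all 4. These are counts of logical cases, not proportions of women.

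**Step 3: how high can the total be in the uncovered case?** Assume each EPDS item is scored 0-3. The article gives 1-3 only as the positive scores on item 10, so this is an assumption. With item 10 at 0, the other 9 items can sum to at most 9 × 3 = 27. Totals from 13 to 27 are then possible with item 10 at 0, and none of them prompts a call by itself under the harms rule.

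**Step 4: ceiling on numbers.** 25 × 3 = 75 planned participants. Only those who report a mental health concern enter the pathway, and only those in the fourth row of the table are affected. The article gives no rate for either, so the actual number cannot be derived.

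**The case against.** The strongest defence is that the two rules serve different situations. The first is an entry screen applied to every woman; the second starts from a reported concern, and the services to be discussed are described differently. On that reading the harms section is tiered: every reported concern goes to ORIGINS whatever the score, and a call is added for self-harm thoughts or traumatic stress. ORIGINS has its own procedures for adverse events, which are cited but not shown, so it cannot be established that the uncovered woman receives less clinical follow-up overall. Nor does the text forbid a call on clinical judgement. The affected group is narrow, and women already at 13 or more on entry had a call then.

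Some of this stands. The woman is not left without any follow-up, the group is probably small, and the article does not show what ORIGINS would do for her.

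The tiered reading, however, is possible but has no support in the text. Women who meet the item 10 or PCL-C trigger receive both the report and the call, so the report was not written as a substitute for the call. The content of the ORIGINS procedures cannot be assumed to include a psychologist's call. Nor is this detail that a condensed article has simply left out: the section sets out its triggers explicitly, with a numerical cut-off for one of the two instruments. The earlier call does not help women who were below the threshold at entry, in whom deterioration would be new.

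**Conclusion.** The concern holds. As written, the harms pathway gives a depression instrument and takes no psychologist action on its total, although the same total prompts a call at screening. One of the two EPDS triggers is missing, which leaves 1 of the 4 combinations uncovered for women with a total of 13 or more.

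The point concerns participant safety. It does not affect the feasibility metrics, the progression criteria, the estimation of standard deviations or any analysis. The report to ORIGINS and the independent monitor reduce the consequence without removing it.

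The conclusion rests on the wording of the two sections alone. The 0-3 item scoring is used only to show the range of totals and is not needed for the finding. It should be fixed before enrolment.

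**What to change.** In Data Monitoring and Harms, add the EPDS total to the call triggers, so that the study psychologist calls any participant with an EPDS total ≥13, or item 10 ≥1, or an abbreviated PCL-C score ≥14. All 4 combinations in the table are then covered.

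This takes one phrase in the text. It needs no new instrument, assessment or staff, because the EPDS is already given at that point and the psychologist is already in place. The running cost is one added call for each screen in which a woman who has reported a concern scores 13 or more with item 10 at 0 and PCL-C below 14.

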## Results

This study was funded in September 2019 and received ethics approval on July 8, 2020. Enrollment to the study will commence in September 2020. A period of 1 year is scheduled for data collection, analysis, and publication of results. The results will inform the design of an adequately powered RCT.

## Discussion

There is a need for scalable, flexible, and accessible interventions to promote the mental health of women during the perinatal period. Such interventions play an important role in supporting maternal resilience across pregnancy, potentially preventing the development of mental health problems and adjustment difficulties in the postpartum period. Although there is evidence to support the use of MBIs for improving psychological health in the perinatal period, data on the feasibility and acceptability of web-based MBIs are limited. Furthermore, little is known about the comparative benefits of alternative meditation training programs such as those that aim to cultivate loving-kindness and compassion. As no prior studies have compared MBIs and CBIs in the perinatal period, this pilot study will provide important insights into how women might differentially experience these interventions. It will also provide data to support the design of a large-scale RCT.

### Strengths

The proposed study has both strengths and limitations. The relative strength of the intervention approach is the involvement of mothers in the development of the intervention conditions. To our knowledge, there is limited literature documenting consumer involvement in the development of meditation-based interventions or in perinatal mental health promotion programs. Furthermore, the proposed trial will collect multiple measures of intervention engagement, experience, acceptability, adherence, perceived benefits, and harm. This comprehensive approach aligns with the recommendations made by Dimidjian and Segal [83] for progressing the clinical science of MBIs. In addition, the study is nested within a large longitudinal birth cohort, enabling future follow-up of study participants and their offspring. Finally, we have prespecified criteria for determining the feasibility of the study and determining whether to proceed with the full-scale RCT. Should the study proceed to a full-scale RCT, this will be one of few randomized trials of MBIs with pregnant women that use a well-matched active control condition.

### Limitations

The situation of this study within a larger longitudinal birth cohort study also has limitations, namely that participants in the study are limited to those who have already consented to participate in a research project with a significant time investment. Accordingly, these women may not be representative of the general population, and insights into the accessibility and scalability of the MMM intervention are thus limited to this group. We propose to address this in the future by conducting consultation with women and service providers at other maternity hospitals not participating in ORIGINS and to study the effectiveness and implementation of the MMM study in women giving birth in these hospitals. A further limitation of the study is the potential confounding due to the capacity of participants in the study to seek psychological treatment while participating. To explore the impact of concurrent treatment, we will measure this at baseline and posttest, with the intention of analyzing these data in a full-scale RCT. Furthermore, it is anticipated that our sample will be heterogeneous with regard to the levels of psychological distress that participants experience and types of other support accessed during the study period. Despite these limitations, we believe that the proposed trial will provide important insights into the potential utility of web-based meditation-based training as a scalable public health intervention for promoting perinatal mental health.

## Appendix

Multimedia Appendix 1 Description of mindfulness and loving-kindness and compassion practices used in the Mums Minds Matter program.

## Abbreviations

ADePT: A process for Decision making after Pilot and Feasibility Trials
CBI: compassion-based intervention
EPDS: Edinburgh Postnatal Depression Scale
JHC: Joondalup Health Campus
LKCT: loving-kindness and compassion training
MBI: mindfulness-based intervention
MMM: Mums’ Mind Matter
PMR: Progressive Muscle Relaxation
RA: research assistant
RCT: randomized controlled trial
